### Research Questions

This project aims to redress the gap in existing gambling service provision by evaluating a theoretically informed and evidence-based JITAI that builds on pilot data provided by the evaluation of *GamblingLess: Curb Your Urge* [115,116]. *GamblingLess: In-The-Moment* is a smartphone-delivered JITAI for people who want to quit or gamble less. It uses EMAs to collect comprehensive and accurate data on the dynamic cognitive processes articulated by the relapse prevention model. The JITAI uses *decision rules* specifying that individuals who are in a state of receptivity (available for treatment) and report a state of cognitive vulnerability characterized by high craving intensity, low self-efficacy, or positive outcome expectancies (*tailoring variables*) in EMAs sent during 3 semirandom times a day (*decision points*) are delivered tailored cognitive behavioral and third-wave interventions targeting these cognitive processes (*intervention options*). The intervention aims to reduce gambling symptom severity in the long term (*distal outcome*), and reduce the likelihood of gambling episodes (*primary proximal outcome*) in the short term via improved craving intensity, self-efficacy, and positive outcome expectancies (*secondary proximal outcomes*). The JITAI is intended for use as a stand-alone or adjunctive treatment during periods of active gambling behavior or as a relapse prevention tool during recovery.

A microrandomized trial (MRT), a form of sequential factorial design in which every participant serves as their own control, will be used to inform the optimization of this JITAI [93,98]. In this MRT, each participant will be randomized to a tailored intervention condition or no intervention control condition at each decision point across a 28-day period [121,122]. The primary aim of the MRT is to explore whether it is worthwhile to deliver a tailored intervention option at a time of cognitive vulnerability. Specifically, the aim is to explore whether, compared with the delivery of no intervention, the delivery of a tailored intervention reduces the probability of a subsequent gambling episode (primary proximal outcome) and improves craving intensity, self-efficacy, and positive outcome expectancies (secondary proximal outcomes). It is hypothesized that the delivery of a tailored intervention will be more effective than no intervention in reducing the probability of a gambling episode and improving craving intensity, self-efficacy, and positive outcome expectancies by the subsequent EMA. Should data allow, secondary exploratory research questions include the following:

*Which type of intervention option is most beneficial at a time of cognitive vulnerability?* Is the delivery of one intervention option (targeting cravings, self-efficacy, or positive outcome expectancies) more likely to reduce the probability of a subsequent gambling episode than the other intervention options?*Under what conditions is the delivery of an intervention option most beneficial?* How do time-variant (EMA) factors (time of day, time of week, craving intensity, self-efficacy, positive outcome expectancies, psychological distress, impulsivity, subjective alcohol intoxication, readiness to change, gambling availability [financial and location], and social context) and time-invariant (preintervention survey) factors (gambling symptom severity, gambling frequency, gambling expenditure, gender, and age) influence the intervention effect on the probability of a subsequent gambling episode?*How do the proximal effects of intervention options change over time as the treatment progresses?* How does the effect of a tailored intervention on the probability of a subsequent gambling episode change over the course of the 28-day MRT?

## Methods

### Ethics Approval

This trial has been approved by the Deakin University Human Research Ethics Committee (2020-304) and registered with the Australian New Zealand Clinical Trials Registry (ACTRN12622000490774).

### Trial Design

MRTs have significant advantages over randomized controlled trials as participants act as their own control group, providing a strong capacity for causal inferences and increased power to detect treatment effects [98]. Moreover, they are designed to facilitate the optimization of JITAIs, which involves determining how a JITAI should be adjusted to make it more effective, efficient, and scalable [98,122,123]. Participants will participate in a 28-day MRT, in which they will be prompted via push notifications on their smartphones to complete a time-based EMA 3 times daily (*decision points*). In this EMA, *tailoring variables* used to determine intervention eligibility include momentary craving intensity, self-efficacy, and positive outcome expectancies. *Decision rules* based on EMA item cut points will determine eligibility for a tailored intervention, which could consist of a craving, self-efficacy, or positive outcome expectancy *intervention option*. Participants will be randomly allocated to either a tailored intervention condition or no intervention control condition at each *decision point* across the 28-day trial period. To maintain the integrity of the MRT evaluation, the JITAI will be evaluated as an entirely *push* intervention during the 28-day MRT period [97,98]. This trial will provide important empirical data that can be used to facilitate the optimization of the JITAI to make it a more effective, efficient, and scalable intervention.

The MRT will be supplemented with (1) a within-group follow-up evaluation to explore the long-term outcomes of the intervention in relation to the primary (gambling symptom severity) and secondary (gambling frequency, gambling expenditure, cravings, self-efficacy, and positive outcome expectancies) outcomes from the preintervention evaluation to the postintervention and 6-month follow-up evaluations as well as the predictors of long-term treatment outcomes and (2) an evaluation of the acceptability of the JITAI using postintervention surveys, app use and engagement indices, and semistructured interviews. An overview of the trial design is shown in Figure 1.

**Figure 1 figure1:**
[figure not shown]
Overview of the *GamblingLess: In-The-Moment* trial design. EMA: ecological momentary assessment; MRT: microrandomized trial.

### Participant Recruitment and Reimbursement

Participants will be recruited across Australia and New Zealand, using a range of strategies, such as web-based advertising (eg, Google Adwords), social media (eg, Facebook and Instagram), gambling-related websites (eg, GambleAware, Gambling Helpline, Gambling Help Online, and Australasian Gaming Council), and advertisements in public places (eg, universities, general practices, health services, mental health services, and alcohol and other drug services). Gambling counseling services and gambling venues may also be requested to assist with participant recruitment. The eligibility criteria will include (1) current Australian or New Zealand residence, (2) ≥18 years of age, (3) installation of the app from an internet-enabled smartphone, (4) willingness to receive notifications from the app, (5) fluency in the English language, and (6) seeking support for one’s own gambling. The target population for *GamblingLess: In-The-Moment* comprises people who want to quit or gamble less. Consistent with a pragmatic design, the intervention will be available to any interested gambler, regardless of the level of gambling symptom severity or whether they are seeking other forms of support or treatment [124]. Moreover, consistent with a harm minimization approach, participants can select abstinence or nonabstinence treatment goals [125-127]. Participants in the trial will be compensated for their time in e-gift vouchers: US $0.70 for each EMA completed and a US $14 bonus if >75% of the EMAs are completed (to a maximum of US $70), US $35 for completion of the postintervention survey, US $50 for completion of the 6-month follow-up survey, and US $35 for the optional semistructured interview.

### Onboarding Protocol

Participants will be required to download *GamblingLess: In-The-Moment* from app stores and provide explicit agreement to the trial plain language statement, as well as the app platform’s terms of use and privacy policy. By agreeing to the terms and privacy policy, participants declare that they have read and understood the plain language statement, are freely participating in the trial according to this statement, meet the eligibility criteria, and understand their privacy rights. They will be required to create an account on the platform by providing the requisite details for the app platform (username, email address, password, and display name). The in-app onboarding protocol will then require participants to read a brief app description and information about how to use the app. They will then be required to indicate whether they are gamblers, family members, or stakeholders in order to complete the preintervention survey (see *Within-Group Follow-up Evaluation*). Finally, they are required to record their mobile number, indicate their interest in being contacted for further research, and indicate their interest in participating in the semistructured interviews. Following this onboarding protocol, the participants will be encouraged to complete their first EMA.

### Distal and Proximal Outcomes

The *distal outcome* of *GamblingLess: In-The-Moment* is the severity of gambling symptoms. The *primary proximal outcome* is reduced probability of a subsequent gambling episode (measured at the subsequent EMA). This outcome will be measured in the EMA using the item, “Have you gambled since the last time you checked in?” with a binary response option (yes or no). The secondary proximal outcomes are improvements in subsequent craving intensity, self-efficacy, and positive outcome expectancies (measured at the subsequent EMA).

### EMA Features

#### Overview

*GamblingLess: In-The-Moment* will use an EMA protocol (Multimedia Appendix 1) employing in-app time-based sampling (ie, semirandomly prompting individuals to input internal states and ecological contexts), which will incorporate event-based sampling (collecting data around specific and discrete gambling episodes). Each EMA, which will take approximately 1 minute to complete, will comprise 10 items measuring momentary internal states and ecological contexts (including the tailoring variables), most of which are recorded on varying 5-point response scales presented in a multiple-choice format. To ensure an accurate record of gambling events, participants will also be administered an event record (Multimedia Appendix 1) in each EMA, in which they will record gambling episodes (primary proximal outcome) and associated expenditure using single items that have been used in previous EMA and ecological momentary intervention gambling research [90,92,115,116].

#### Decision Points

During the 28-day MRT, participants will be prompted via push notifications to complete an EMA delivered through the app 3 times daily at random times during the prespecified periods: morning (8:30 AM-11 AM), afternoon (1 PM-3:30 PM), and evening (5:30 PM-8 PM; Figure 1). At each EMA notification, participants can auto-launch the EMA via the notification or app. Participants will be allowed 2 hours to complete an EMA to preserve the momentary nature of the intervention while accommodating the potential for possible unavailability (eg, driving and working) of the participant at the initial prompt time [98,128].

#### Tailoring Variables

The tailoring variables for *GamblingLess: In-The-Moment* include momentary craving intensity, self-efficacy, and positive outcome expectancies measured during each EMA (Multimedia Appendix 1). The craving item was adapted from the first item of the Gambling Symptom Assessment Scale [129], the self-efficacy item was adapted from the Brief Situational Confidence Questionnaire-Gambling [130], and the positive outcome expectancy item was adapted from the Gambling Outcome Expectancy Scale [69]. The JITAI will tailor the type, timing, and amount of support to individual needs [94-96,99,100] (Figure 1). The tailoring variable data received from each participant will be used to individualize treatment by repeatedly selecting the *type* of intervention content (craving, self-efficacy, or positive outcome expectancies). The flexible collection of tailoring variable data will allow for the *timely* individualization of intervention options at specific moments when individuals are especially in need of support but not when they do not need support or are unreceptive to support. Finally, the dosage or *amount* of support will be tailored to individual needs via an intervention loop, whereby participants who continue to require support after completing an intervention activity will be offered additional support.

#### Additional EMA Items

Additional single items measuring other momentary internal states and ecological contextual factors highlighted by the relapse prevention model [13,15] will be included in each EMA to explore the conditions under which the JITAI is most effective: psychological distress (based on the distress thermometer: Psychosocial Distress Practice Guidelines) [131], readiness to change (based on the gambling readiness ruler) [132], subjective alcohol intoxication (based on the Subjective Effects of Alcohol Scale) [133], impulsivity (based on an EMA item from the Momentary Impulsivity Scale) [134], social context (based on an EMA item measuring social context for alcohol use) [135], financial gambling availability (based on an EMA item assessing money for preferred products) [136], and location gambling availability (based on an EMA item assessing cigarette availability [137]) (Multimedia Appendix 1).

#### Welcome and Reminder Protocol

The following contact protocol will be adopted to enhance EMA compliance during the 28-day MRT: (1) an automated welcome email to all participants following onboarding, (2) a reminder email to participants who fail to complete onboarding or fail to complete an EMA for more than 48 hours following onboarding, and (3) a reminder telephone call by clinically or qualitatively trained research fellows to participants who still fail to complete onboarding or an EMA in the subsequent 48-hour period (with a follow-up SMS message if no answer or second follow-up email if no valid phone number was provided). Participants who fail to complete an EMA following this protocol will receive no further contact but (as long as they complete onboarding and at least one EMA and have some engagement with app-intervention activities) will be contacted to request completion of the postintervention and 6-month follow-up surveys.

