### Within-Group Follow-up Evaluation

A within-group evaluation of outcomes over a 6-month follow-up period will supplement the MRT to (1) evaluate within-group change over a longer period and (2) explore predictors of longer-term treatment outcomes (including app use over the 6-month follow-up period). Although the preintervention survey will be automated via the app before beginning the 28-day MRT period, participants will be prompted by email to complete the postintervention and follow-up surveys via Qualtrics (Qualtrics XM). Descriptive and covariate measures will include participant type (gambler, family member or friend, and clinician, researcher, or policy maker), sociodemographic characteristics, problem gambling activities, intended gambling behavior (measured using the Timeline Follow-Forward, a novel adaptation of the Timeline Follow-Back [148]), and other help-seeking (measured using the Help Seeking Questionnaire [149]). The primary outcome will be gambling symptom severity (measured using the Gambling Symptom Assessment Scale [129]), and secondary outcomes will include gambling frequency and expenditure (measured using a timeline follow-back at the preintervention evaluation, the EMA event record data at the posttreatment evaluation, and single items at the 6-month evaluation) and the cognitive processes targeted by the intervention: craving severity (measured using the Penn Gambling Craving Scale [25]), self-efficacy (measured using the Brief Situational Confidence Questionnaire-Gambling [130]), and positive outcome expectancies (measured using the Excitement, Escape, and Money subscales of the Gambling Outcome Expectancies Scale [69]; Multimedia Appendix 4). Each evaluation will be completed in approximately 10 to 15 minutes. Ideally, follow-up evaluation surveys will also be conducted 12 and 24 months after the intervention, but this will be dependent on obtaining additional funding.

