A follow-up protocol will be implemented to enhance the completion of the postintervention and 6-month follow-up surveys: (1) an email requesting survey completion, (2) a reminder email requesting survey completion within a week to participants who fail to complete the survey in the subsequent 1-week period, and (3) up to 2 reminder telephone calls by clinically or qualitatively trained research fellows to participants who fail to complete the survey in the subsequent 3-week period (with a follow-up SMS text message if no answer or a further follow-up email if no valid phone number was provided). An advance notice email will also be sent 1 week before the 6-month surveys are sent. At each time point, the option to complete the survey over the phone with a trained research fellow will be offered. Participants who fail to complete the surveys following this protocol will receive no further contact, but participants failing to complete the postintervention survey will be contacted to request the completion of the 6-month follow-up survey.

During the 6-month follow-up evaluation period, tailored intervention content will be available to participants on demand. Although Nahum-Shani et al [94] defines JITAI designs as a *push* intervention approach, participant-determined features may accommodate conditions in which participants know when and what type of support is required, promote autonomy by facilitating agency and control, reduce waste and disruption, generalize learned skills, and maintain therapeutic gains [94,97-99,101,150]. During this period, participants will not receive push notifications to complete EMAs and the microrandomization protocol will not be applied (ie, all participants will be allocated to the tailored intervention condition, with the no intervention control condition turned off). However, they will be able to access tailored intervention content via participant-initiated EMAs (ie, they can complete an EMA at any time, which will direct them to tailored intervention content). This approach has been adopted to encourage participants to incorporate coping skills in their everyday lives when they recognize states of vulnerability or opportunity and are motivated to initiate access to support [97-99,101]. The degree to which app use across the 6-month follow-up period influences longer-term treatment outcomes will be explored.

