To explore the long-term outcomes of the intervention (within-group follow-up evaluation), distal outcomes will be assessed using GEE by regressing the outcome of interest (eg, gambling symptom severity) on a variable denoting time (ie, preintervention, postintervention, 6-month follow-up variables) and covariates. The factors associated with longer-term treatment outcomes will also be explored using GEE by regressing the outcome of interest (eg, clinically significant change in gambling symptom severity) with selected preintervention, postintervention, and app use variables (eg, the number of participant-initiated EMAs completed in the 6-month follow-up period). Where appropriate, missingness will be addressed using multiple imputation, with appropriate accounting for the multilevel nature of the data (eg, see multilevel multiple imputation [155]).

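### Participants who stop answering EMAs are sent the follow-up surveys only if they used intervention activities, so follow-up of early stoppers is selected on engagement, exposure and symptom level

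*Protocol article*

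**What the plan says.** The Welcome and Reminder Protocol sets out an email and then a telephone call for people who are not completing EMAs. It then states: "Participants who fail to complete an EMA following this protocol will receive no further contact". There is one exception. Such people "will be contacted to request completion of the postintervention and 6-month follow-up surveys", but only "as long as they complete onboarding and at least one EMA and have some engagement with app-intervention activities". The one-EMA condition shows that the rule reaches people who started and then stopped, as well as those who never began.

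The Within-Group Follow-up Evaluation section says that "participants failing to complete the postintervention survey will be contacted to request the completion of the 6-month follow-up survey". That keeps the 6-month request open after a missed postintervention survey. It does not lift the engagement condition.

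The follow-up evaluation is meant to "evaluate within-group change over a longer period", with gambling symptom severity as its primary outcome. Under Statistical Analyses, that outcome is regressed on time (preintervention, postintervention, 6 months) by GEE. On missing data the section says: "Where appropriate, missingness will be addressed using multiple imputation", allowing for the multilevel structure. Nothing in the article limits the follow-up conclusions to people who engaged.

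**The concern.** The distal outcome has no control group, so the completeness of follow-up is one of the few protections its estimate has. The preintervention survey is part of in-app onboarding. A participant who finishes onboarding and then drops away without using an activity therefore has a baseline score, but is never asked for an outcome. That gap is created by the contact rule and comes on top of ordinary non-response.

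The rule also selects on more than willingness. Three kinds of early stopper fail the engagement condition:

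- people who were offered activities and did not use them;
- people who never exceeded a cut point and so were never eligible for an activity;
- people whose few eligible decision points all went to the control condition, which provides no activities.

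At stake are the mean change in gambling symptom severity and the individual classification into recovered, improved, unchanged or deteriorated. The acceptability ratings are also touched, because they are collected in the same postintervention survey. The trial is described as pragmatic and open to any interested gambler, so a reader would take these results to describe everyone enrolled.

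**Working it through.** **The plan's own figures.** Sample Size assumes 40% attrition from 200, and 200 × (1 − 0.40) = 120 reproduces. That figure serves the microrandomized comparison. The article gives no sample size for the follow-up evaluation and no figure for the share excluded by the contact rule.

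**Step 1: who can meet the engagement condition.** Three sections, read together:

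- Decision Rules: a participant below every cut point is eligible for no intervention.
- Microrandomization Protocol: an eligible participant has a 75% chance of the tailored condition and a 25% chance of control.
- No Intervention Control Condition: control gives a message and no activities.

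During the 28 days, activities are therefore reached only by exceeding a cut point and being randomized to the tailored condition.

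**Step 2: the part due to chance.** For a participant who stops after k eligible EMAs, with independent randomization at each, the probability of never having been offered an activity is 0.25^k.

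| k | Probability never offered an activity |
|---|---|
| 1 | 25% |
| 2 | 0.25² = 6.25% |
| 3 | 0.25³ = 1.6% |

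An early stopper whose completed EMAs never exceeded a cut point has k = 0 and was certainly never offered one.

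**Step 3: effect on mean change.** Let q be the share excluded by the rule, with true mean change m_e, and let contacted participants have mean change m_c. The mean for everyone is (1 − q)m_c + q·m_e. An estimate that rests on contacted participants differs from it by

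m_c − [(1 − q)m_c + q·m_e] = q(m_c − m_e) = q × d.

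Both q and d are assumptions, since the article gives neither:

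| q | d | Bias, q × d |
|---|---|---|
| 0.05 | 0.2 SD | 0.01 SD |
| 0.10 | 0.5 SD | 0.05 SD |
| 0.40 (all assumed attrition, an upper bound) | 0.8 SD | 0.32 SD |

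The formula assumes that everyone contacted responds. If every onboarded participant were invited, q from this rule would be 0 and ordinary non-response would remain.

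**Step 4: what imputation can do.** Excluded participants who finished onboarding have baseline data, so they could be kept in the model. No one who both stopped and did not engage is surveyed, however, so their outcomes must be borrowed from stoppers who engaged or from people who kept responding. That requires change to be the same, given the observed variables, in people who left without engaging. The trial's data cannot check this.

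**The case against.** Several points on the other side are sound, and they limit the finding.

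- **Some non-users are followed.** A reader might infer that nobody without activity use is ever surveyed. That is not so. The condition applies only to people who stop completing EMAs. Those who keep completing them are still invited, whether they skip the activities, never exceed a cut point or draw control.
- **The rule governs contact, not analysis.** A reader might infer that these participants are removed from the analysis set. The article does not say so; it specifies GEE with imputation where appropriate.
- **The pilot's attrition does not estimate q.** A reader might set the 19% and 39% under Sample Size beside a worst-case formula, 1/(1 − q) − 1, which gives 25% overstatement at q = 20%. The 39% counts from completion of baseline and the 19% from later download, whereas here the preintervention survey sits inside the app. Both figures are general attrition, and leavers who used an activity are still invited. The formula also assumes no change at all in anyone excluded, and full response if they were asked.
- **The direction is not proven.** Some early stoppers who were never flagged as vulnerable may be doing well. It also does not follow that an association between app use and outcome is inflated: removing people with no use and no change can leave the slope unchanged or even lower it.
- **The gain is limited.** These people have already not responded to the reminders, so many may not answer a survey. The follow-up is also a supplement to the microrandomized trial.

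What remains is a stated rule that withholds follow-up from part of the enrolled group on grounds related to exposure and symptom level. Imputation narrows the problem but does not remove it.

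**Conclusion.** The point holds in a limited form. For participants who stop completing EMAs, the survey request depends on engagement with activities, and the chance to engage depends on symptom level and random assignment. The uncontrolled estimate of change in gambling symptom severity is therefore exposed to selection by design among early stoppers.

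The size is q × d, with both quantities unknown. It is 0.01 to 0.05 SD in the two modest scenarios and 0.32 SD in a deliberately extreme one. Overstated improvement is likely if people who do not engage improve less, but the article does not establish that. The microrandomized primary comparison is not affected. The change is worth making because it is cheap and removes an avoidable source of missing data; it does not call the main design into question.

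**What to change.** Delete the one-EMA and activity-engagement conditions from the Welcome and Reminder Protocol. Send both the postintervention and the 6-month survey, under the existing survey follow-up procedure, to every participant who completed onboarding and the preintervention survey. Not following people who never finished onboarding is unobjectionable.

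If the rule is kept, or follow-up has already closed, state that the follow-up conclusions do not cover early stoppers who did not engage with activities.

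The cost is some extra emails and reminder calls, plus vouchers of US $35 and US $50 per extra responder for the two surveys. Email addresses and mobile numbers are already collected at onboarding. Response in this group is likely to be low, so the change would reduce the selection without removing it.
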